## Abstract

**Figure ivae045-F1:**
[figure not shown]

Latest research has indicated a potential adverse effect on graft patency rates and clinical outcomes with skeletonizing the left internal thoracic artery. We aim to provide a prospective, randomized, multicentre trial to compare skeletonized versus pedicled harvesting technique of left internal thoracic artery concerning graft patency rates and patient survival. A total of 1350 patients will be randomized to either skeletonized or pedicled harvesting technique and undergo surgical revascularization. Follow-up will be performed at 30 days, 1 year, 2 years and 5 years after surgery. The primary outcome will be death or left internal thoracic artery graft occlusion in coronary computed tomography angiography or invasive angiography within 2 years (+/- 3 months) after surgery. The secondary outcome will be major adverse cardiac events (composite outcome of all-cause death, myocardial infarction and repeated revascularization) within 1 year, 2 years and 5 years after surgery. The primary end point will be compared in the modified intention-to-treat population between the two treatment groups using Kaplan–Meier graphs, together with log-rank testing. Hereby, we present the study protocol of the first adequately powered prospective, randomized, multicentre trial which compares skeletonized and pedicled harvesting technique of left internal thoracic artery regarding graft patency rates and patient survival.

## OBJECTIVES

Since the landmark study by Loop *et al.* in 1986 [1], the left internal thoracic artery (LITA) is the preferred bypass conduit to the left anterior descending artery (LAD), owing to its survival benefit over the saphenous vein graft (SVG), which has also been noted in other observational studies [2, 3] and in 1 small randomized trial [4].

Since occlusion of the proximal LAD more often leads to fatal myocardial infarction than occlusion of non-LAD coronary vessels (except from the left main coronary artery), the LAD has an extremely important role in myocardial revascularization [1].

Therefore, current European and American guidelines [5, 6] recommend the use of the LITA to the LAD to improve patient outcomes.

Two techniques exist for surgical harvesting of the LITA during coronary artery bypass grafting (CABG): pedicled and skeletonized harvesting techniques [7]. While a pedicle contains the artery, together with its accompanying veins, fatty tissue and endothoracic fascia, in skeletonized harvesting technique, only the artery is harvested.

Skeletonizing the internal thoracic artery (ITA) may be more time-consuming and more challenging, but it provides a longer graft and better free flow [8]. Furthermore, various studies have described the reduced incidence of sternal wound infections with the skeletonized harvesting technique [9–13]. On the other hand, when only one ITA is used, skeletonization does not provide any additional effect on preventing sternal wound complications [9]. Deep sternal wound infections in particular are associated with increased mortality and morbidity [14], but they are caused by multiple factors, not solely by the ITA harvesting technique [15]. Lazar *et al.* was able to eliminate any form of sternal wound infection by 3 perioperative measures: perioperative intravenous antibiotics, topical vancomycin applied to the sternal edges and tight glycaemic control [16].

Besides the potential beneficial effects, skeletonizing the ITAs is thought to be more prone to injury [17]. Latest research by Lamy *et al.* and Gaudino *et al.* has noted a potential adverse effect of skeletonizing the LITA on graft patency rates and clinical outcomes [18, 19]. In a post hoc analysis of the COMPASS trial, Lamy *et al.* saw a significantly reduced short-term graft patency at 1 year and a significantly higher risk for major adverse cardiac events (MACE) at 23 months after CABG for skeletonized harvesting technique. In a post hoc analysis of the ART trial, Gaudino *et al.* did not provide data on graft patency rates, but at 10 years, the risk for MACE was significantly higher for skeletonized versus pedicled ITA grafts. A difference in the 10-year mortality rate was not seen. Interestingly, the impaired outcome was only observed with surgeons who had enrolled fewer than 51 patients in the study, implying that the surgeon’s experience plays a key role. Furthermore, a significant learning curve has been described for LITA graft harvesting [20].

To date, no adequately powered randomized trial has been performed to investigate the influence of the harvesting technique of ITA on graft patency rates and clinical outcomes. Due to the ongoing debate on the potential adverse outcome of skeletonized harvesting technique of ITA, only prospective randomized trials will show whether skeletonizing of ITA is a safe procedure or contains potential adverse effects.

Therefore, with the HARVITA trial, our goal is to provide a prospective, randomized, multicentre trial to compare patency rates following skeletonized versus pedicled harvesting technique of LITA.

## METHODS

### Study design

The HARVITA trial is a 2-arm, prospective, randomized, multicentre clinical trial, the goal of which is to evaluate the impact of the LITA harvesting technique on patency rates. All patients who are referred for isolated CABG will be screened for inclusion and exclusion criteria. Informed consent will be required for eligible patients. Patients will be randomized to skeletonized or pedicled harvesting technique of LITA. Coronary computed tomography angiography (cCTA) will be performed to evaluate LITA graft status 2 years (+/- 3 months) after surgery. Follow-up will be performed at 30 days, 1 year, 2 years and 5 years after surgery.

### Primary hypothesis

The primary hypothesis is as follows: The harvesting technique of LITA (skeletonized versus pedicled) is associated with a difference in the rate of death or LITA graft occlusion within 2 years (+/- 3 months) after surgery.

## ELIGIBILITY

### Inclusion criteria

Primary isolated CABG patients with multivessel disease (defined as ≥ 70% stenosis of the LAD and ≥ 50% stenosis of the circumflex and the right coronary territory, with or without  ≥ 50% stenosis of the left main artery)

### Exclusion criteria

Age > 80 yearsPlanned CABG without using the LITAPreoperative mediastinal radiation therapyEmergency operationMinimally invasive coronary artery bypass surgeryAny concomitant cardiac or non-cardiac proceduresPrevious cardiac surgeryKnown contrast agent allergySevere stenosis of the left subclavian artery/left-sided subclavian steal syndromeChronic kidney disease (glomerular filtration rate < 60 ml/min/1.73m^2^)Life expectancy of less than 5 yearsPregnancyHyperthyroidismIodine allergy

### Intraoperative exclusion criteria

Y/T graft off the LITA graftLITA sequential graftingLITA target vessel other than LAD

### Randomization, stratification and enrolment

All patients having a planned isolated CABG procedure are screened according to the inclusion and exclusion criteria. Those patients who are eligible and have given informed consent will be randomized to 1 of the 2 treatment arms (skeletonized or pedicled harvesting technique).

Patients will be randomized in a 1:1 fashion. Permuted block randomization with variable block sizes and stratification by centre will be performed with a web-based randomization system in order to achieve an equal distribution in both groups. Log will be held for all screened patients with reasons for inclusion and exclusion.

### Surgical procedure

Surgery should take place within 4 weeks of randomization. It will be carried out via a median sternotomy and either on-pump or off-pump. Harvesting of the LITA is performed by surgeons who are technically capable of both harvesting techniques and who have harvested at least 50 ITAs. The LITA is harvested with electrocautery or with a harmonic scalpel, independently of allocated harvesting techniques and according to the established method in each centre. Only topical, but not intravasal, application (in order to decrease the risk of a potential endothelial damage) of spasmolytic agents will be used. If the patient is randomized to the skeletonized harvesting technique, only the LITA itself will be harvested. If the pedicled harvesting technique is used, the LITA, together with its accompanying veins and parts of the endothoracic fascia, will be harvested, creating a 1- to 2- cm broad pedicle. Through an incision in the pericardium, the LITA is brought intrapericardially and then anastomosed with running suture to the LAD. In case of pedicled harvesting technique, the pedicle is stabilized without tension at the height of the anastomosis with sutures at the surface of the heart, to avoid twisting of the pedicle. Any target vessel for the LITA other than the LAD is against protocol. For the LITA, a sequential or T/Y graft configuration is not allowed. The LITA is primarily used as an in situ graft. The remaining diseased coronary vessels (≥1.5 mm and target vessel stenosis ≥50%) will receive SVG, radial artery (RA) or right ITA (RITA). The SVG can be harvested using either the open (conventional or no-touch) or the endoscopic technique. The RA can be harvested in open or endoscopic technique; in both cases as a pedicle. The RITA can be harvested using either the skeletonized or the pedicled technique, independent of the randomization process. Surgeons are encouraged to attach the proximal part of the SVG and/or the RA to the ascending aorta. It is recommended not to use the RA that has been used for coronary angiography (CAG) prior to the operation. It is also recommended to anastomose the RA to a target vessel with high-grade stenosis. After de-cannulation and administration of protamine, transit time flow measurements are used for final evaluation of all grafts. All transit time flow measurements are performed at a mean arterial pressure of 70 to 80 mmHg, as far distally as safely possible. The mean graft flow (ml/min), pulsatility index and mean arterial blood pressure (mmHg) are recorded.

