## STATISTICS

### Study design and objectives

This is a 2-arm, prospective, randomized, observer-blinded, multicentre clinical trial, designed to evaluate the impact of harvesting technique of LITA on graft occlusion-free survival. The primary end point is defined as death or LITA graft occlusion identified via cCTA or invasive angiography within 2 years (+/− 3 months). The secondary end points include MACE- (composite outcome of all-cause death, myocardial infarction and repeated revascularization) free survival, occlusion rate and other graft-related outcomes. LITA graft occlusion-free survival and MACE-free survival are treated as time-to-event variables with observation time ranging from date of surgery (time zero) to either date of event or censoring date.

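### Randomizing at consent, up to 4 weeks before an open operation, lets the harvesting surgeon be chosen with the arm known; randomize at surgery, after the harvester is named

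*Protocol article*

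**What the plan says.** Protocol article, Randomization, stratification and enrolment: "Those patients who are eligible and have given informed consent will be randomized to 1 of the 2 treatment arms". On method: "Permuted block randomization with variable block sizes and stratification by centre will be performed with a web-based randomization system". Centre is the only stratification factor named.

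Surgical procedure: "Surgery should take place within 4 weeks of randomization". On who operates: "Harvesting of the LITA is performed by surgeons who are technically capable of both harvesting techniques and who have harvested at least 50 ITAs". The same section restricts the LITA target to the LAD and rules out sequential and T/Y configurations. It leaves the right-sided artery open: "The RITA can be harvested using either the skeletonized or the pedicled technique, independent of the randomization process".

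Study design and objectives (Statistics): "This is a 2-arm, prospective, randomized, observer-blinded, multicentre clinical trial". The blinding described is that of the image readers.

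Objectives: skeletonizing is said to be possibly slower and harder. Of an earlier post hoc analysis, the article reports that "the impaired outcome was only observed with surgeons who had enrolled fewer than 51 patients in the study". It also cites a learning curve for LITA harvesting. Its own reading of that earlier result is given as "implying that the surgeon’s experience plays a key role".

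Study population and Efficacy analysis: the primary comparison uses the modified intention-to-treat set, which requires that surgery took place and that a LITA was joined to the LAD. Both are settled after randomization.

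**The concern.** The sequence generation is sound. The weakness is the point in the patient's pathway at which it is used. Allocation is made at consent, and the operation may follow weeks later. In between, a centre can roster any surgeon who meets the entry requirement. If it knows the arm when it does so, it has a reason to match surgeon to technique, and the article supplies that reason: one technique may be harder, and experience is thought to drive results.

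If that happens, experience differs between arms because of a choice made after allocation, and the trial compares technique plus operator instead of technique alone. The centre-stratified log-rank test does not remove this, because the selection takes place within centres. Later adjustment for surgeon cannot fully repair it either, since the surgeon would then be a consequence of the arm.

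A second route is attrition. The longer the gap, the more operations can be cancelled or changed after allocation, and those patients are not in the primary analysis set.

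**Working it through.** **What is fixed before allocation, from the article**

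| Item | Fixed before allocation? |
|---|---|
| LITA target and configuration | Yes, by rule: LAD only, no sequential or T/Y graft; breaches are intraoperative exclusions |
| Energy device | Yes, by centre practice, whatever the arm |
| Harvesting surgeon | No rule shown beyond the entry requirement |
| RITA technique | No, either technique is allowed |
| Having surgery at all | No, and it decides entry to the primary analysis set |

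The harvester and cancellations are thus the routes that reach the primary outcome.

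**The plan's own figure.** Inputs from the sample size section: 4% pedicled, 8% skeletonized, alpha 0.05 (two-sided, from the efficacy hypotheses), power 0.80, 558 per group. Hazard ratios below are pedicled versus skeletonized, as in that section.

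- HR = ln(0.96)/ln(0.92) = 0.0408/0.0834 = 0.490, matching the stated 0.49.
- Expected events = 558 × (0.04 + 0.08) = 67.
- Freedman: power = Φ(√events × (1 − HR)/(1 + HR) − 1.96) = Φ(2.804 − 1.96) = 0.801.

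This reproduces the 558 per group. The 62 events stated beside it follow from Schoenfeld's formula; that difference does not affect this point.

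**Illustration of steering.** Assumed, not in the documents: less-experienced harvesters do half of all cases and have r times the event risk of experienced ones. They do a share s of pedicled and 1 − s of skeletonized cases.

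With r = 2, the experienced-harvester risks are 4%/1.5 = 2.67% and 8%/1.5 = 5.33%. With s = 60%:

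- Pedicled: 2.67% × 1.6 = 4.27%. Skeletonized: 5.33% × 1.4 = 7.47%.
- HR = ln(0.9573)/ln(0.9253) = 0.562; events = 558 × 0.1173 = 65.5.
- Power = Φ(2.270 − 1.96) = 0.622.

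The same formulas for other assumptions:

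| r | Split (pedicled/skeletonized) | Rates | Power |
|---|---|---|---|
| 2 | 55/45 | 4.13% v 7.73% | 0.719 |
| 2 | 60/40 | 4.27% v 7.47% | 0.622 |
| 2 | 70/30 | 4.53% v 6.93% | 0.406 |
| 1.5 | 60/40 | 4.16% v 7.68% | 0.700 |
| 3 | 60/40 | 4.40% v 7.20% | 0.515 |

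**No true effect.** Take 6% in both arms, r = 2, 60/40. The experienced-harvester risk is 6%/1.5 = 4%, so the arms show 4% × 1.6 = 6.4% and 4% × 1.4 = 5.6%. Events are 558 × 0.12 = 67, and the shift in the test statistic is 0.563. The rejection probability is Φ(0.563 − 1.96) + Φ(−0.563 − 1.96) = 0.081 + 0.006 = 0.087, against 0.05.

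**Opposite direction.** If less-experienced harvesters instead did 40% of pedicled and 60% of skeletonized cases (r = 2), the rates would be 2.67% × 1.4 = 3.73% and 5.33% × 1.6 = 8.53%. The HR would be ln(0.9627)/ln(0.9147) = 0.43, which exaggerates the assumed effect. The sign of the bias depends on how centres would roster, and the article does not say.

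**The case against.** The best reply is that the article gives a maximum interval from randomization to surgery and does not say when the theatre team learns the arm. Disclosure and rostering may be settled in a full protocol that is not shown. This stands in part: it cannot be said that the allocation is known to the team for 4 weeks. But the article does fix the randomization at consent and describes no delayed release, so the plan as written allows the choice.

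Second, all harvesters must master both techniques and have at least 50 harvests, the energy device follows centre practice, and the image readers are blinded to the arm. These limit the problem. The 50-harvest rule, however, is a floor: it counts both techniques together and leaves experience above it unequal.

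Third, the risk ratios and splits are invented for illustration, and no steering has been shown. That is correct. Likewise, nothing shows that cancellations would differ by arm; if they do not, they cost only numbers, for which the plan already raises 558 to 675 per group.

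A reader might also infer that LITA configuration is open to arm-aware choice, or that RITA technique biases the primary result. The article does not support either. The configuration is set by rule. RITA technique bears mainly on sternal wound complications, a secondary outcome tested only descriptively, and reaches the primary outcome at most through death.

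**Conclusion.** The concern holds as a design weakness that is cheap to remove, not as a demonstrated bias. The article sets randomization at consent, allows up to 4 weeks to surgery, leaves the operator unblinded and stratifies by centre only. Its own background makes operator experience a plausible driver of the result. Choice of harvester with the arm known is therefore possible, as are cancellations after allocation that leave the primary set.

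Size and direction are unknown. Under the main illustration, power is about 62% instead of 80%, or the type I error about 9% instead of 5%. Across the illustrated assumptions, power runs from 72% down to 41%. A reader might conclude that the plan will mask harm from skeletonizing; the documents do not support that, because they contain no information on how centres would assign harvesters, and steering the other way would exaggerate the difference.

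**What to change.** In Randomization, stratification and enrolment and in Surgical procedure, replace the timing rule with wording such as: *Consent and screening may take place up to 4 weeks before surgery. Randomization is done on the day of surgery or at the earliest on the working day before. The web system releases the allocation only after the centre has entered the named harvesting surgeon and any planned RITA use and technique.*

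Add that any later change of harvester or plan is recorded with its reason, that harvester is reported by arm, and that any analysis by surgeon uses the entry made before allocation.

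The cost is a wording change and a few mandatory fields in the existing web system, with no extra patients or procedures. The theatre learns the technique at short notice and someone must log in at that time. Both are manageable, because every harvester must already be capable of both techniques. The change should be in place before enrolment.

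It reduces decisions made with the arm known but does not abolish them: a harvester can still be changed, though visibly, and the intraoperative exclusions still follow allocation.

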
### Recommendations to prevent sternal wound infections

Sternal wound infections are associated with high mortality and morbidity [14]. The European Association for Cardio-Thoracic Surgery and the American Association for Thoracic Surgery provide guidelines for the prevention and treatment of sternal wound infections [14, 21]. We recommend applying the following measures to both treatment groups (skeletonized and pedicled harvesting technique) in order to prevent the occurrence of sternal wound infections:

Routine screening for nasal carriers of *Staphylococcus aureus;*Applicaton of topical mupirocin to the nares in all patients without negative screening for staphylococcus using a nasal swab within 24 h of the operation and for up to 5 days postoperatively;Administer continuous insulin therapy to keep the blood glucose level < 180 mg/dl within the first 24 h after surgery or for the duration of the stay in the intensive care unit;Administer a cephalosporin (either cefuroxime or cefazolin) as a first choice 60 min prior to the skin incision and for up to a maximum of 72 h (individual institutional protocols are accepted);Use a topical application of vancomycin to the bone edges immediately after a median sternotomy and prior to sternal closure;Avoid the use of bone wax.

### Postoperative treatment

Postoperative treatment will be carried out according to local standards and current guidelines [22]. Treatment with antiplatelet agents should be restarted within 24 h after the operation, in case there is no concern regarding surgical bleeding. If a RA was used as a graft, the decision to use spasmolytic medication (agent, duration and time of initiation) will be left to local practice. Secondary prophylaxis should be carried out according to current guidelines [5, 23, 24]. We generally recommend the use of aspirin as an antiplatelet agent (indefinitely), the use of angiotensin-converting-enzyme inhibitors/angiotensin receptor blockers (sartane), the use of a beta blocker and the use of a statin for guideline-conforming secondary prophylaxis. In case of dual antiplatelet therapy (off-pump, previous acute coronary syndrome, previous elective/acute coronary stent implant), we recommend the use of aspirin in combination with clopidogrel to ensure uniformity.

## OUTCOME MEASURES

### Primary outcome

Death or LITA graft occlusion in cCTA or invasive angiography within 2 years (+/- 3 months) after surgery.

### Secondary outcomes

MACE-free survival (composite outcome of all-cause death, myocardial infarction and repeated revascularization) within 1 year, 2 years and 5 years after surgery.

Additional secondary outcomes include the following:

Death/LITA graft occlusion (in cCTA or invasive angiography)/intraoperative LITA graft injury within 2 years (+/- 3 months) postoperatively;LITA graft occlusion (and LITA graft dysfunction) in cCTA or invasive angiography at 2 years (+/- 3 months);LITA graft occlusion at cCTA or invasive angiography for patients with cCTA or invasive angiography for clinical reasons;Repeated revascularization at 2 years and 5 years after surgery;Repeated revascularization of the left anterior descending artery (LITA target vessel revascularization) at 2 years and 5 years after surgery;Sternal wound complications at 1 year after surgery;Composite end point of the LITA graft occlusion/dysfunction (cCTA or invasive angiography), myocardial infarction and repeat revascularization within 2 years (+/- 3 months) after surgery;Perioperative outcome at 30 days.

### Further analyses

Primary and secondary end points for male versus female sex;Primary and secondary end points according to the severity of target vessel stenosis (moderate 50 - <70%, severe ≥70% or occlusion);Competing risk analyses.

### Follow-up

Patients will receive cCTA examinations at 2 years (+/- 3 months) postoperatively. One week prior to the cCTA scan, blood samples (glomerular filtration rate, creatinine and thyroid stimulating hormone for the upcoming cCTA; LDL-cholesterol and HbA1c for follow-up) will be collected. At 30 days, 1 year, 2 years and 5 years postoperatively, phone calls will be used for follow-up (Table 1). cCTA should be performed within a time span of 6 months (-3 months to + 3 months) for 2 year’s cCTA. If cCTA or invasive angiography is performed for clinical reasons (e.g. signs of acute or chronic ischaemia, acute myocardial infarction, heart failure or recurrence of symptoms) prior to the above-mentioned time interval (> 3 months prior to the cCTA at 2 years) and the LITA graft is not occluded, cCTA will be performed according to protocol. If cCTA or invasive angiography is performed for other reasons prior to the above-mentioned time interval (> 3 months prior to cCTA at 2 years) and the LITA graft is occluded, cCTA will not be performed, and the findings of the cCTA/CAG will be used for statistical analysis. If CAG is performed for other reasons within the above-mentioned time intervals (≤ 3 months prior to the cCTA at 2 years) and the LITA graft does or does not show LITA graft occlusion, the cCTA will not be repeated, and the findings of the CAG will be used for statistical analysis. In the case of occlusion or dysfunction of other grafts rather than the LITA, patients with clinical symptoms and/or pathological findings noted from non-invasive testing should be referred for invasive angiography. This decision will be left to the clinical assessment of the participating centres.

**Table 1: ivae045-T1:** The follow-up process

Follow-up	30 days	1 year	2 years	5 years
Telephone interview	x	x	x (2 years + 3 months)	x
cCTA			x (2 years +/− 3 months)	

cCTA: coronary computed tomography angiography.

